## Abstract

**Background:**

T1 colorectal cancer (CRC) without histological high-risk factors for lymph node metastasis (LNM) can potentially be cured by endoscopic resection, which is associated with significantly lower morbidity, mortality and costs compared to radical surgery. An important prerequisite for endoscopic resection as definite treatment is the histological confirmation of tumour-free resection margins. Incomplete resection with involved (R1) or indeterminate (Rx) margins is considered a strong risk factor for residual disease and local recurrence. Therefore, international guidelines recommend additional surgery in case of R1/Rx resection, even in absence of high-risk factors for LNM. Endoscopic full-thickness resection (eFTR) is a relatively new technique that allows transmural resection of colorectal lesions. Local scar excision after prior R1/Rx resection of low-risk T1 CRC could offer an attractive minimal invasive strategy to achieve confirmation about radicality of the previous resection or a second attempt for radical resection of residual luminal cancer. However, oncologic safety has not been established and long-term data are lacking. Besides, surveillance varies widely and requires standardization.

**Methods/design:**

In this nationwide, multicenter, prospective cohort study we aim to assess feasibility and oncological safety of completion eFTR following incomplete resection of low-risk T1 CRC. The primary endpoint is to assess the 2 and 5 year luminal local tumor recurrence rate. Secondary study endpoints are to assess feasibility, percentage of curative eFTR-resections, presence of scar tissue and/or complete scar excision at histopathology, safety of eFTR compared to surgery, 2 and 5 year nodal and/or distant tumor recurrence rate and 5-year disease-specific and overall-survival rate.

**Discussion:**

Since the implementation of CRC screening programs, the diagnostic rate of T1 CRC is steadily increasing. A significant proportion is not recognized as cancer before endoscopic resection and is therefore resected through conventional techniques primarily reserved for benign polyps. As such, precise histological assessment is often hampered due to cauterization and fragmentation and frequently leads to treatment dilemmas. This first prospective trial will potentially demonstrate the effectiveness and oncological safety of completion eFTR for patients who have undergone a previous incomplete T1 CRC resection. Hereby, substantial surgical overtreatment may be avoided, leading to treatment optimization and organ preservation.

*Trial registration* Nederlands Trial Register, NL 7879, 16 July 2019 (https://trialregister.nl/trial/7879).

## Background

### Background and rationale

The implementation of colorectal cancer (CRC) screening programs worldwide has led to a significant increase in the detection of T1 CRC [1–5]. These early cancers have a limited risk for lymph node metastasis (LNM), varying between 1 and 16% depending on histopathological risk features and thus can potentially be cured by endoscopic resection [6–9]. Endoscopic resection is an attractive treatment option compared to radical surgery because of its low morbidity and mortality rates and substantially lower costs [10–14]. However, endoscopic resection can only be accepted as final treatment when the risk for LNM or local recurrence do not outweigh surgery associated mortality (1.7%) and disease recurrence despite oncologic surgery (2 to 5%) [10–14]. Treatment recommendations either to proceed with additional oncologic surgery or surveillance alone after endoscopic resection, mainly depend on the presence of histopathological risk factors for local recurrence and LNM [15]. Previous studies have shown that the risk of local recurrence and LNM is very low in absence of the following high-risk features: poor differentiation, lymphovascular invasion, deep submucosal invasion (≥ 1000 µm), high-grade tumor budding (grade 2 or 3) and a positive resection margin (R1/Rx resection) [6, 7, 9, 16–18]. If one of these high-risk features is present, patients are currently counselled for additional oncological surgery according to current guidelines [19, 20].

Positive polypectomy margin status (i.e. positive resection margin < 0.1 mm (R1) or indeterminate resection margin (Rx) is considered a strong risk factor for residual disease in the colon wall and local recurrence [6, 21–26]. Current guidelines therefore advise additional oncological surgery, even in the absence of unfavourable histological factors [18, 27]. However, even in the presence of high-risk factors for LNM, residual disease is noted in less than 20% of patients undergoing additional surgery. Therefore, a surgical resection can be considered potential overtreatment, especially in patients without increased risk for LNM [6, 21, 22, 24]. Despite this apparent surgical overtreatment, a certain number of patients are at risk of having residual cancer with risk of cancer dissemination, when additional oncologic surgery is not performed. Among these patients, CRC-related mortality was reported to be as high as 42% [15]. However, the potential impact of implementation of strict surveillance protocols on earlier diagnosis of cancer recurrence to allow for curative salvage therapy is currently unknown.

In daily practice, real-time endoscopic recognition of T1 CRC is challenging. Recent Dutch studies demonstrated that endoscopists recognized only 22–39% of all diagnosed T1 CRC as being cancer before endoscopic resection [28, 29]. As result of suboptimal diagnosis, 41% missed potential endoscopic cure due to the selection of inappropriate endoscopic techniques [15, 30]. Conventional polypectomy techniques like piecemeal or *en bloc* snare coagulation often hamper adequate histological assessment leading to uncertainty about the completeness of excision or the presence of histological risk factors. To achieve definite histopathological confirmation about radicality of the resection, or a second chance for radical resection in case of remaining cancer within the bowel wall, an additional endoscopic *en bloc* resection of the previous resection scar might be an attractive strategy. Until recently, no safe endoscopic *en bloc* re-resection technique was available for the re-resection of scar tissue or non-lifting, incomplete resected lesions. The introduction of endoscopic full-thickness resection (eFTR) has expanded the therapeutic endoscopic armamentarium and several large-scale clinical studies have now established its feasibility and safety for complex colorectal lesions [31–34]. The eFTR-technique allows a transmural local excision of the scar and therefore can potentially serve as a valid option for curative completion treatment following incomplete T1 CRC resection, potentially avoiding unnecessary surgical risks [35–40].

eFTR is currently increasingly used for this indication in daily practice. Our previous multicenter feasibility study showed that eFTR of scars of previous R1/Rx resected T1 CRC was technically feasible in 85% with promising short-term results. [25] However, long-term oncologic safety has not been established. By implementing completion eFTR in a prospective national cohort study followed by protocolized surveillance, we aim to assess its feasibility and long-term oncologic safety after previous incomplete resection of low-risk T1 CRC.

### Objectives

This project aims to investigate the feasibility and oncological safety of endoscopic full-thickness resection (eFTR) as minimal invasive completion treatment after previous R1/Rx endoscopic resection of low-risk T1 CRC. We hypothesize that completion eFTR is feasible in ≥ 80% of patients with a low risk of luminal cancer recurrence < 2%.

### Trial design

This nationwide prospective observational multicenter study aims to investigate the feasibility and oncological safety of eFTR as completion treatment after previous potential incomplete resection of low-risk T1 CRC. Patients referred for completion eFTR for low-risk T1 CRC with positive resection margins < 0.1 mm (R1) or indeterminate margins (Rx) are eligible for participation in this prospective cohort study. Patients will be followed by protocolized surveillance during 5 years.

## Methods

### Study setting

Prospective observational multicenter study in academic and non-academic hospitals throughout the Netherlands.

### Eligibility criteria

#### Inclusion criteria

Patients meeting all of the following criteria will be invited for participation in the study:Recent polypectomy/(p)EMR/ESD of T1 CRC *without* the following histological high-risk features*:oPoor differentiationpLymphovascular invasionqTumor budding grade 2/3This recent polypectomy/(p)EMR/ESD for T1 CRC resulted in positive resection margins < 0.1 mm (R1) or indeterminate resection margins (Rx)The resection scar after polypectomy/EMR/ESD is clearly recognized at endoscopy, either by a tattoo or by detecting a scar in the colorectal segment where no other polypectomies were performedDiameter of the original lesion ≤ 30 mmDiameter of the scar and/or residual lesion ≤ 15 mmInterval between index polypectomy/EMR/ESD and additional eFTR at most 12 weeksStaging computed tomography (CT) of thorax and abdomen without local lymph node or distant metastases. In case of rectal location an additional magnetic resonance imaging (MRI) of the pelvis is performed at which no local suspicious lymph node(s) detected. If the target lesion is visible on MRI, rectal location is defined as location distal from the sigmoid take off. If not visible on MRI, rectal location is defined as < 15 cm from anal verge on endoscopy.Written informed consent provided

*Before inclusion in this study, eligible histology needs to be centrally reviewed by one of the two expert gastrointestinal pathologist. In case of any doubt on the presence of high-risk features, both expert pathologist will have a case discussion in order to reach consensus.

#### Exclusion criteria

Patients meeting any of the following criteria will be excluded from participation in this study:If lymphovascular invasion and/or tumor budding grade 2/3 cannot be assessed after prior polypectomy/(p)EMR, patients are *NOT* eligible for inclusionThe patient is known with at least one of the following conditions:oActive inflammatory bowel disease (IBD) in the colorectumpSynchronous advanced CRC (defined as CRC in the 5 years before detection of T1 CRC, or elsewhere in the colorectum at the time of detection of T1 CRC)Index lesion located < 5 cm of the anal verge or with involvement of the valvula Bauhini or appendiceal orificeAge < 18 yearsPregnancy

### Who will take informed consent?

Local gastroenterologists, gastroenterology fellows, research nurses or other members of the study team in the participating centers will inform eligible patients about the study aims, the prospective data collection, the eFTR procedure and follow up procedures. All patients will receive an informed consent form. Patients will be given as much time as needed to make an informed decision regarding participation.

### Outcomes

The primary outcome is to assess the 2- and 5- year local luminal tumor recurrence rate after scar resection by eFTR following a previous R1/Rx resection of low-risk T1 CRC.

The secondary outcomes are:to assess the feasibility of completion eFTR, defined as a macroscopic complete en bloc scar excision in > 80% of casesto assess the percentage of curative eFTR resections, defined as no residual cancer in the scar or in case any residual cancer a R0 resection for T1 CRC without high-risk features (poor differentiation, lymphovascular invasion and/or high-grade tumor budding (grade 2 or 3)to assess the presence of scar tissue and/or complete scar excision at histopathologyto assess the procedure-related adverse event rate and safety of eFTR compared to oncologic surgery in a historical patient-cohort for T1 CRCto assess the 2- and 5- year locoregional nodal and/or distant tumor recurrence rateto assess the 5-year disease-specific survival rate and overall survival rateto assess the 2- and 5-year luminal, nodal and distant tumor recurrence rate in patients not meeting our inclusion criteria, but who did undergo eFTR completion treatment followed by strict surveillance and are included in our observational arm

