#### Histopathology handling

The resection specimen is stretched and pinned down on paraffin or cork before immersed into formalin. Histopathological analysis is performed by a gastrointestinal pathologist according to daily clinical practice. In case of presence of residual adenocarcinoma, deep and lateral resection margins will be assessed as well as all histological risk features (differentiation grade, depth of invasion, lymphovascular invasion and tumor budding (grade 2 or 3)).

In the eFTR specimen, the pathologist will assess the presence of reactive changes compatible with scar tissue in the specimen. Definite histopathological confirmation of complete scar resection is known to be difficult and might not always be possible. In case the pathologist is not able to histologically confirm complete scar resection, further treatment will be based on the macroscopic completeness of scar excision and patients will be followed according to protocol.

In addition, central review of all resected eFTR specimens will be performed after all patients are included in the study. The central review will be performed by two independent expert gastrointestinal pathologists. In this review, the presence of neoplasia, scar tissue and evaluation of completeness of excision regarding both neoplasia and scar will be evaluated by both expert pathologists. In cases without consensus, meetings will be organized to discuss discrepancies to reach consensus. In case no consensus can be reached, a third expert pathologist will be consulted.

H&E slides of all resected eFTR specimens will be collected from the different laboratories and digitalized at the Amsterdam UMC for review. After digitalizing the slides will return to the laboratories to ensure the completeness of pathology archives and optimal patient care.

In case of unexpected findings, the treating physician will be informed to discuss further treatment options with the patients after colorectal MDT discussion. Outcomes of these cases will be recorded in the study database.

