### Follow-up

In case the specimen of eFTR contains residual cancer with high-risk features and/or incomplete eFTR resection (Rx/R1), the case should be discussed in a colorectal MDT board for further treatment options depending on histological and endoscopic findings. The same accounts for cases in which completion eFTR of the scar was technically impossible. The outcomes, subsequent treatment and further follow-up procedures of these cases will be recorded in the study database. In this prospective cohort study, the follow-up schedule will be in line with the Dutch Guidelines (in preparation).

For all detected local, nodal and/or distant tumor recurrences during follow-up, the outcomes and subsequent treatment will be recorded in the study database.

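### The no-residual-cancer limb of the curative eFTR definition has no completeness condition, so a partial scar excision with a cancer-free specimen counts as curative

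*Protocol article*

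**What the plan says.** In the protocol article, Outcomes, a curative eFTR resection is "defined as no residual cancer in the scar or in case any residual cancer a R0 resection for T1 CRC without high-risk features". The high-risk features are then listed in brackets.

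Two neighbouring secondary outcomes cover completeness, and neither is linked to the curative label. Feasibility is judged by macroscopically complete en bloc excision of the scar, with a threshold of more than 80%. A further outcome records whether scar tissue is present, and whether the scar is completely excised, on histology.

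Histopathology handling accepts a limit on what the pathologist can show: "Definite histopathological confirmation of complete scar resection is known to be difficult and might not always be possible". In that situation "further treatment will be based on the macroscopic completeness of scar excision and patients will be followed according to protocol". The same section plans a central review of every eFTR specimen by two independent expert pathologists, covering neoplasia, scar tissue and completeness of excision of both.

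Follow-up says that for "incomplete eFTR resection (Rx/R1), the case should be discussed in a colorectal MDT board for further treatment options". Cases in which eFTR was technically impossible are handled in the same way.

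**The concern.** The definition has two limbs. The limb for residual cancer asks for R0 margins and no high-risk features. The limb for no residual cancer asks for nothing about how much of the scar was removed. If the specimen holds only part of the scar and that part is free of cancer, the case satisfies the first limb, although the part left behind was never examined.

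This sits badly with the stated reason for the procedure in Background and rationale: "To achieve definite histopathological confirmation about radicality of the resection, or a second chance for radical resection in case of remaining cancer". A partial excision without cancer gives no confirmation of radicality, and it is not a radical second resection either. Such a case can fail the feasibility outcome and the scar-excision outcome and still count as curative. If the MDT rule in Follow-up is meant to include incompletely excised, cancer-free scars, the same patient would be scored as cured while further treatment is being discussed.

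What is at stake is the meaning of one secondary percentage. Its name is one that readers, and the guideline group the article hopes to reach, would take at face value.

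**Working it through.** **The plan's own figure.** The article gives no target, expected value or sample size for the curative percentage, so there is nothing to reproduce. The figures of 137 and 153 patients belong to the recurrence endpoint.

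**Reading the definition case by case (resections performed, specimen obtained)**

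| Specimen | Status as written |
|---|---|
| Scar completely excised, no cancer | Curative, as intended |
| Residual T1 cancer, R0, no high-risk features | Curative, as intended |
| Residual cancer, R1/Rx or high-risk features | Not curative, as intended |
| Scar partly excised, removed part cancer-free | Curative, because no condition excludes it |
| No scar tissue in the specimen, no cancer | Not stated |

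**Direction.** Adding a completeness condition can only remove cases from the curative group. With a fixed denominator the rate as written is therefore never below the rate with the condition. If the affected cases are instead taken out of the denominator, the rate as written is still never lower, because every affected case was scored curative.

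**Size, for illustration only.** Inputs, both assumed:

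- *m*, the share of resected specimens that are cancer-free but incompletely excised or without scar: 5% to 20%. The documents give no such figure.
- *r*, the share of patients with residual cancer: 5% to 20%. The top of the range borrows from Background and rationale, where "residual disease is noted in less than 20% of patients undergoing additional surgery".

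The illustration also assumes that every residual cancer in a completely excised scar is non-curative, which ignores those removed R0 without high-risk features.

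- Rate as written = (1 − *m*)(1 − *r*) + *m*
- Rate if affected cases count as non-curative = (1 − *m*)(1 − *r*). The excess is *m*.
- Rate if affected cases leave the denominator = 1 − *r*. The excess is (1 − *m*)(1 − *r*) + *m* − (1 − *r*) = *m* × *r*.

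| *m* | *r* | As written | Counted non-curative | Left out of denominator |
|---|---|---|---|---|
| 5% | 5% | 95.25% | 90.25% (excess 5 points) | 95.0% (excess 0.25) |
| 10% | 10% | 91.0% | 81.0% (excess 10) | 90.0% (excess 1.0) |
| 15% | 10% | 91.5% | 76.5% (excess 15) | 90.0% (excess 1.5) |
| 20% | 20% | 84.0% | 64.0% (excess 20) | 80.0% (excess 4.0) |

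The excess thus runs from about 0.3 to 4 points under exclusion, and up to *m* itself if affected cases count as non-curative. Residual cancers removed R0 without high-risk features would raise the curative rate among complete excisions. That makes the exclusion figures smaller and leaves the other column's excess at *m*.

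**The case against.** Several points on the other side are sound.

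- **The wording is narrower than it may seem.** A reader might infer that any cancer-free specimen is curative, including one that missed the scar. The text speaks of no cancer in the scar, which can be read as presupposing that scar is there. The documents support the partial-excision case. For a specimen without scar they support only the statement that its class is not given.
- **A large inflation cannot be taken from the feasibility figures.** The article reports that "eFTR of scars of previous R1/Rx resected T1 CRC was technically feasible in 85% with promising short-term results" and hypothesises feasibility of at least 80%. A reader might turn the remaining 15-20% into 10-20 points of inflation, or into 153 × 0.10 × 0.20 ≈ 3 to 153 × 0.20 × 0.20 ≈ 6 patients with cancer left behind yet scored curative. The documents do not support this. A procedure that was technically impossible yields no specimen to misclassify. The 80% is a hypothesis and not an observed rate. The 153 includes a 10% allowance that covers technically impossible cases. The residual-disease figure is stated to hold even with high-risk factors present, so it is not specific to this low-risk cohort.
- **The components are reported anyway.** Macroscopic completeness and histological scar status are separate outcomes, so the missing information can be recovered from the full set of results. It is only the single percentage that cannot distinguish a clear scar from an unsampled one.
- **Missed targets are made less likely by design.** The scar must be clearly recognised and at most 15 mm across, endoscopists need at least 10 personal procedures, and the site is inspected after resection.
- **The article is condensed.** A fuller document may hold the denominator and the handling of unconfirmable specimens, and their absence here is not counted as a fault. The definition itself is stated in the article, however, and as stated it admits partial excisions.

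These points limit the size and importance of the problem. They do not supply the missing condition.

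**Conclusion.** The point holds as a defect in the wording of one secondary endpoint. As written, a partial scar excision with a cancer-free specimen is curative, and a specimen without scar tissue has no stated class. The upward direction follows from the definition alone. The size does not follow from the documents: the 0.3 to 4 points, and the ceiling equal to the affected share, rest on the assumed 5-20% ranges.

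The outcome is unpowered and has no target. The safety conclusion rests on luminal recurrence, whose definition and analysis set do not use the curative label, so it is unaffected.

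**What to change.** Reword the outcome so that a resection is curative if either:

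- (a) the scar was excised en bloc and macroscopically completely, and no residual cancer is found; or
- (b) residual T1 CRC was resected R0 without high-risk features.

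Report cancer-free specimens with macroscopically incomplete excision, or with no scar tissue at central review, as a separate indeterminate category. Keep that category in the denominator of all resections performed.

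Histological confirmation of complete scar excision should not be a condition for (a), because Histopathology handling says it cannot always be obtained. Instead, show the curative rate with and without that confirmation, using the central review already planned.

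The cost is a change of wording and one extra row in a table. Macroscopic completeness is needed for the feasibility outcome, and scar status is part of the central review, so no new data are required. The reported curative percentage will be somewhat lower. The change concerns how outcomes are classified and leaves patient management as it is.
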